**Recruitment**

The study will be advertised by printed flyers throughout the endocrine clinic of Baqiyatallah Hospital. Flyers will also be handed to practitioners caring for potential participants as well. All advertising material will have the contact number and email address of our research team on it, and interested patients will contact us directly if they wish to hear more about the trial and wish to schedule a telephone screen for eligibility assessment. Afterwards, the eligible and interested individuals will be asked to sign the written informed consent and the first appointment will be booked. During the first appointment, the consented subjects undergo a screening procedure to make sure they meet the inclusion criteria. The eligible subjects will be enrolled in the trial and randomized to appropriate study groups. The participant recruitment period is planned for 8 months and will continue until 56 patients are participated in the study.

**Methods: Assignment of interventions (for controlled trials)**

**Allocation: Sequence generation**

Block randomization method with a block size of 4 will be used in the present study. Random number sequences will be drawn from https://sealedenvelope.com/.

**Allocation concealment mechanism**

In terms of allocation concealment, unique codes derived from the mentioned website will be written on each supplement box by a hospital staff who is not aware of the aims of the study.

**Implementation**

The treatment codes will remain with the staff until the final data analysis and/or an emergency situation. After checking the inclusion and exclusion criteria and baseline measurements, each participant will be given a supplement box.

**Blinding**

All the participants, researchers, practitioners, and outcome assessors will be blinded to the treatment allocation. In the event of an emergency situation where the knowledge of the treatment allocation is critical for further management of the participant, the hospital staff will be given access to unblinding the codes assigned to each participant. The treatment code would be communicated to the medical personnel in charge of the treatment but should not be recorded or verbally disclosed in any of the study documents or to the patient. The emergency unblinding and the reason will be further reported.

**Methods: Data collection, management, and analysis**

**Data collection methods**

Schedule of outcome assessment is represented in Figure 2. The primary outcomes include serum levels of TSH and fT4. The secondary outcomes are BP, quality of life, and depression. The information on anthropometric indices, PA, and dietary intake will be collected to control the potential confounders and covariates. The primary and secondary outcomes will be conducted at baseline and the end of the study (10^th^ week) for all participants. Adherence will be checked every week.

***Laboratory investigations***

All participants will be asked to fast 8-12 hours overnight for blood sample collection (10 ml) at the baseline and the end of study. The samples will be collected into tubes (without anticoagulant and in EDTA in the tubes) and centrifuged at 3000 rpm for 10 min (Hettich D-78532; Tuttlingen, Germany) to obtain serum or plasma. The serum samples (3 ml) will be stored at - 80º c until the end of the trial. Plasma and the remaining serum will be used to determine TSH and fT4 (Pishtazteb Eliza kits, Tehran, Iran).

***Blood Pressure***

BP will be measured at baseline and end of the study by an assessor under the following conditions: After 5 minutes of rest in a quiet place, the participants will be sitting without crossed legs and unsupported back and arms. The BP of the participants will be measured in the left arm at the elbow in a flexed position on the chair by a digital barometer (Omron, Tokyo, Japan). The mean of three readings will be recorded (1-minute interval between them).

***Quality of life***

Short Form Health Survey (SF-36) questionnaire will be used to assess health-related quality of life (HRQOL) in the present study (35). This questionnaire has been translated and validated in the Iranian population (36). SF-36 questionnaire measures 8 domains of health including physical functioning (10 items), role limitations due to physical problems (4 items) and emotional problems (3 items), bodily pain (2 items), general health perceptions (5 items)), vitality (4 items), social functioning (2 items), and perceived mental health (5 items). Also, there is a single item for health transition that provides an indication of perceived change in general health status over a one-year period. Summing the score of the 36 items, an overall score ranging from 0 to 100 will be obtained. The higher the score of SF-36, the higher quality of the participant’s life.

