**Outcomes**

Schedule of outcome assessment is represented in Figure 2. The primary outcomes include serum levels of TSH and fT4. The secondary outcomes are BP, quality of life, and depression. The information on anthropometric indices, PA, and dietary intake will be collected to control the potential confounders and covariates. The primary and secondary outcomes will be conducted at baseline and the end of the study (10th week) for all participants and change from baseline will be reported. Adherence will be checked every week.

**Figure 1**. Flow chart of the study design.

Eligible hypothyroid adults (women/men) with written informed consent will be recruited from Baqiyatallah hospital and will be enrolled in this RCT (n=56)

Randomize to two parallel treatment groups for 10 weeks (70 days):

1) synbiotic supplement (n= 28)

2) placebo (n= 28)

1

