***Depression***

The Beck Depression Inventory II (BDI-II), a self-rating instrument, will be used to assess depression among the participants of the present study (37). An Iranian version of BDI-II has been developed and its reliability and validity has been assessed in the Iranian population (38). The BDI-II consists of 21 sets of statements about depressive symptoms in the last 15 days that are rated on a 0 to 3 ordinal scale, yielding total scores ranging from 0 to 63. The suggested thresholds for levels of severity are as follows: 0-13, minimal/no depression; 14-19, mild depression; 20-28, moderate depression; and 29-63, severe depression.

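### The SF-36 total is defined as a sum of 36 items on a 0 to 100 scale: the sum includes the one-year health-transition item, and a plain sum does not have that range

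*Protocol*

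**What the plan says.** The Protocol lists quality of life among the secondary outcomes: "The secondary outcomes are BP, quality of life, and depression" (Data collection methods). The Outcomes section sets two assessments and reports the difference: "The primary and secondary outcomes will be conducted at baseline and the end of the study (10th week) for all participants and change from baseline".

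The Quality of life section gives the domains and their item counts: "physical functioning (10 items), role limitations due to physical problems (4 items) and emotional problems (3 items") and "bodily pain (2 items), general health perceptions (5 items)), vitality (4 items), social functioning (2 items), and perceived mental health (5 items"). It then adds, apart from those domains, that "there is a single item for health transition that provides an indication of perceived change in general health status over a one-year period".

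The scoring rule follows: "Summing the score of the 36 items, an overall score ranging from 0 to 100 will be obtained". The direction is fixed by: "The higher the score of SF-36, the higher quality of the participant’s life".

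The section gives no response options or item codes, and no step for reversing, averaging or rescaling. The eight domains are described, but no domain score is defined.

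**The concern.** The scoring sentence has two faults that can be seen from the section itself.

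- **Content.** The total takes in an item that the Protocol itself places outside the eight domains. That item already measures change, and over a year, whereas the outcome is the change in current state over 10 weeks.
- **Range.** Adding up 36 item scores does not give the stated scale unless a further step is applied, and none is stated.

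What is at stake is the meaning of one secondary outcome. Its mean, SD and change are to be reported (Statistical methods), and it is part of the trial's hypothesis (Objectives). Two analysts who follow the sentence could produce scores on different scales, and neither could be set safely beside other SF-36 results.

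**Working it through.** **Inputs.** Item counts, stated range and transition item: Protocol, Quality of life. Timing: Protocol, Outcomes. Comparison scale: Protocol, Depression. Response options are not given, so anything that depends on them is marked as an assumption.

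**1. Which items are summed?**
Domain items: 10 + 4 + 3 + 2 + 5 + 4 + 2 + 5 = 35. Adding the transition item: 35 + 1 = 36. A 36-item sum therefore includes the transition item.

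**2. Can the stated range of 0 to 100 be reproduced?**

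| Coding | Range of a plain sum of 36 items |
|---|---|
| Every item 0 to k, k = 1, 2, 3, 4, 5 | 0 to 36k: 0–36, 0–72, 0–108, 0–144, 0–180 |
| Every item coded from 1 | minimum 36 × 1 = 36, never 0 |
| Every item already on 0–100 | 0 to 36 × 100 = 3600 |
| Mixed levels, set A (assumption), from 1 / from 0 | 36–149 / 0–113 |
| Mixed levels, set B (assumption), from 1 / from 0 | 36–161 / 0–125 |

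The assumed numbers of levels, in the Protocol's order of domains with the transition item last, are:

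- Set A: 10×3 + 4×2 + 3×2 + (6+5) + 5×5 + 4×6 + 2×5 + 5×6 + 5 = 149. Coded from 0: 149 − 36 = 113.
- Set B: 10×3 + 4×5 + 3×5 + (6+5) + 5×5 + 4×5 + 2×5 + 5×5 + 5 = 161. Coded from 0: 161 − 36 = 125.

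None of these gives 0 to 100. A zero-based sum that ends at exactly 100 would need an average item maximum of 100/36 = 2.78. Leaving the transition item out does not rescue the range: 113 − 4 = 109 and 125 − 4 = 121.

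**3. Comparison within the Protocol.** For the BDI-II, the items are "rated on a 0 to 3 ordinal scale, yielding total scores ranging from 0 to 63". With 21 items, 21 × 3 = 63, so that range follows from its coding. The SF-36 range does not follow from anything stated.

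**4. Does the transition item fit the outcome?** Its recall window is one year, about 52 weeks. At week 10, 52 − 10 = 42 of those weeks (42/52 = 81%) lie before the intervention. At baseline all of them do. Subtracting the baseline answer from the week-10 answer takes a change of a change.

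**5. How much does it weigh?** With equal item weights, 1/36 = 2.8%. On the assumed zero-based sums, 4/113 = 3.5% or 4/125 = 3.2%. If the item did not move at all, a change in the 35-item mean would be carried into the 36-item mean at 35/36 = 97.2% of its size.

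**The case against.** The best reply is that the sentence is loose shorthand. The section fixes a 0 to 100 range and says that higher is better. Together these imply that items are to be recoded and the total rescaled. The section also cites a validated Iranian version whose scoring is not visible here. If a rescaled sum is meant, the range fault is one of wording only, since a linear rescaling leaves the p-values of a t-test or ANCOVA unchanged. Detailed recoding syntax is also something a protocol may leave to a statistical analysis plan. All of this stands as far as the range is concerned. It does not remove the transition item, because the Protocol counts 36 items, and a stated rule that conflicts with its own range is more than missing detail.

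A reader might infer three stronger things that the documents do not support:

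- **That items will be added unreversed, so that effects partly cancel.** The Protocol gives no response options and does not describe an unrecoded sum. Its statement on direction points the other way.
- **That the domains are wrongly weighted, 5:1 for physical against social functioning (10 items against 2).** That ratio holds only if all items share one scale. On the assumed set A codes the spans are 10 × 2 = 20 and 2 × 4 = 8, or 2.5:1. In any case, weighting by item count is a property of every item total and a matter of preference, not an error.
- **That the outcome is bound to be scored wrongly.** With item-level answers it can be rescored, and the intended scoring may be sounder than the sentence.

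**Conclusion.** The concern holds in a limited form. The inclusion of the transition item follows from the Protocol's own counts and needs no assumption. The mismatch between a plain sum and 0 to 100 is firm for uniform whole-number coding and for items already on 0–100. For mixed response levels it rests on assumed options (0–113 to 0–125, or 36–149 to 36–161). If the sentence means a sum followed by rescaling, only the transition item remains as a fault of substance.

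The numerical effect is small, about 3% of the total. It is confined to one secondary outcome and does not touch TSH, FT4 or the sample size. It is still worth correcting, because the sentence is the only definition the Protocol gives of this outcome and cannot be carried out as written.

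**What to change.** Replace the scoring sentence with a rule that:

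1. recodes every item to 0–100 with higher meaning better;
2. averages the recoded items within each of the eight domains, using the 35 domain items, so that each domain score runs from 0 to 100;
3. reports the health-transition item separately and keeps it out of any total;
4. if one overall figure is kept as the quality-of-life outcome, defines it in advance as either the mean of the eight domain scores or the mean of the 35 recoded items. Both run from 0 to 100.

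The cost is a few sentences and the scoring syntax. The questionnaire, the visits and the data collected stay the same.

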***Depression***

The Beck Depression Inventory II (BDI-II), a self-rating instrument, will be used to assess depression among the participants of the present study (37). An Iranian version of BDI-II has been developed and its reliability and validity has been assessed in the Iranian population (38). The BDI-II consists of 21 sets of statements about depressive symptoms in the last 15 days that are rated on a 0 to 3 ordinal scale, yielding total scores ranging from 0 to 63. The suggested thresholds for levels of severity are as follows: 0-13, minimal/no depression; 14-19, mild depression; 20-28, moderate depression; and 29-63, severe depression.

***Anthropometric indices***

Weight will be measured using a pre-calibrated digital scale (Seca, Germany) to the nearest 0.1 kg. Height will be measured standing up without shoes using a tape measure. Body mass index (BMI) will be calculated by dividing weight (kg) by squared height (m). Waist circumference (WC) will be measured by wrapping the tape measure around the widest part of the stomach, across belly button.

***Physical activity***

The short version of International Physical Activity Questionnaire (IPAQ-SF), which is suitable for adults 15 to 69 years of age, will be used to assess PA in this research (39). IPAQ-SF has acceptable reliability and validity among the Iranian population (40). IPAQ consists of four generic items which reflect on the previous 7 days’ activities (walking, moderate (such as leisure cycling), vigorous activities (such as aerobics), and time spent sitting) and the score within each activity category is reported as minutes per week (min/week) by a Metabolic Equivalent of Task (MET) energy expenditure. The following formula will be used to calculate the PA (MET·min·wk−1): MET level × duration × frequency per week. The results of IPAQ-SF will categorize into 3 levels (vigorous-intensity activity, moderate-intensity activity, low intensity activity) (52). This is a self-report questionnaire and the participants will fill IPAQ-SF.

***Dietary intake***

Dietary intake at the baseline and the end of the study will be recorded using 24-hour dietary recall (completed for 2 weekdays and 1 weekend to account for day-to-day variation). This questionnaire is a structured questionnaire to capture detailed information about all foods and beverages consumed by the respondent in the past 24 hours. The participants will be interviewed by a blinded interviewer to the study allocation. This interviewer encourages the participants to remember the exact type and amount of foods they have eaten by asking proper questions. A blinded expert dietitian to study allocation will review all the completed 24-hour dietary recalls. Dietary intake data will be analyzed using Nutritionist IV software (Version II) to estimate the energy and the amount of macronutrients and micronutrients eaten.

**Data management**

Data entry will be performed along with the sampling. Data will be inserted to an excel sheet by the researcher and will include only the codes, not the names of the participants. This excel file will be stored until the statistical analysis at the end of the trial.

**Statistical methods**

Before statistical analysis, all data will be reviewed in terms of accuracy and completeness. Data will be analyzed using SPSS software (IBM Corp. Released 2016. IBM SPSS Statistics for Windows, Version 24.0. Armonk, NY: IBM Corp). For all analyses, a P value < 0.05 will be considered statistically significant. The normality of data will be checked by the Shapiro-Wilk W Test, P-P and Q-Q plots. All variables will be reported as mean ± SD for before, after the intervention and changes (after minus before). Baseline characteristics of quantitative biochemical and demographic variables will be compared between the two groups by independent sample t-test. The difference between the two groups regarding qualitative variables will be assessed by Chi-square test. Analysis of Covariance (ANCOVA) will be performed to eliminate the effect of confounders. Changes from the base-line to post-intervention within the groups will be illustrated through a paired t-test or Wilcoxon signed-rank test. GraphPad Prism software will be used to draw graphs and illustrate the results (GraphPad Prism version 8.0.0 for Windows, GraphPad Software, San Diego, California USA, [www.graphpad.com](http://www.graphpad.com)).

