**Objectives**

Primary Objectives:

Comparing the mean changes in serum levels of free thyroxine (FT4) and TSH as representatives of thyroid function, between the synbiotic and placebo groups and within the two groups before and after the intervention.

Secondary Objectives:

Comparing the mean changes in systolic blood pressure (SBP), diastolic blood pressure (DBP), depression, and quality of life between the synbiotic and placebo groups and within the two groups before and after the intervention. Also, other data including age, weight, height, body mass index (BMI), physical activity (PA), dietary energy and macronutrient intake, education, career, marital status, duration of the disease, dose of levothyroxine, and type of hypothyroidism (immune and non-immune-related) will be gathered to be taken into account as confounders.

Hypothesis:

10 weeks of synbiotic supplementation will significantly improve serum levels of thyroid hormones, depression, quality of life, SBP and DBP in hypothyroid patients.

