**Sample size**

The sample size was calculated with G-power software version 3.1.9.2. To calculate the sample size, the study of Talebi et al. (29) was used, which was an 8-week clinical trial with two parallel groups. The sample size was calculated considering the probability of the first type error equal to 0.05 (α = 0.05, significance), and the probability of the second type error equal to 0.80 (β = 0.2, power). In this study, the mean change ± standard deviation of placebo and synbiotic groups regarding TSH levels after 8 weeks of intervention were 0.08 ± 0.09 mIU/L and 0.028 ± 0.09 mIU/L, respectively. In this study, in order to observe 0.28 mIU/L difference in serum TSH levels between the two groups at the end of the study, a sample size of 24 patients in each group is required. According to an expected 15% loss to follow-up, the final sample size included in each group will be 28 patients.

[figure not shown]

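### TSH and fT4 are both primary, with no test order or success rule and P < 0.05 for every analysis, so either the primary type I error exceeds 5% or the stated power does not describe the trial

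*Protocol*

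**What the plan says.** The Outcomes section of the protocol states: "The primary outcomes include serum levels of TSH and fT4". Data collection methods repeats this, and the schedule in Figure 2 lists both hormones as primary. The primary objective also names them together: "Comparing the mean changes in serum levels of free thyroxine (FT4) and TSH as representatives of thyroid function". None of these places ranks one above the other.

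The primary objective covers two kinds of comparison, "between the synbiotic and placebo groups and within the two groups before and after the intervention". Statistical methods then applies one threshold to everything: "For all analyses, a P value < 0.05 will be considered statistically significant". It gives no adjustment, no testing order, and no statement of what counts as success on the primary objective.

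The Sample size section uses "probability of the first type error equal to 0.05 (α = 0.05, significance" and a power of 80%, and its source data are "regarding TSH levels after 8 weeks of intervention were 0.08 ± 0.09 mIU/L and 0.028 ± 0.09 mIU/L, respectively". No effect, standard deviation or power is given for fT4.

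**The concern.** With two primary outcomes, the reader needs to know what result makes the trial positive. There are two possible rules, and they have different consequences.

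- **Either outcome suffices.** Two chances at 0.05 give a family-wise error above 0.05.
- **Both are required.** The error is controlled, but the trial must succeed on an outcome for which it was never sized.

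The protocol does not choose between them. A significant fT4 with a null TSH, or the reverse, could therefore be reported as a positive primary result after the data are seen.

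The within-group comparisons add to the problem. They belong to the primary objective and are tested at the same threshold. Under Interventions, both groups also receive advice on diet and physical activity, so a change within the synbiotic group is not by itself evidence for the supplement.

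**Working it through.** **Inputs**

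- Primary outcomes: 2, TSH and fT4 (Objectives, Outcomes).
- Level per test: 0.05 (Statistical methods). Sidedness is not stated; two-sided is assumed, with critical value 1.96.
- Sizing: TSH only, alpha 0.05, power 80%, 24 per group before loss to follow-up (Sample size). The text reads "the probability of the second type error equal to 0.80 (β = 0.2, power"; I take 0.80 as the power and 0.2 as the type II error.
- Correlation between the two test statistics: not given, so a range is shown.

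**Step 1: the plan's own figure.** The normal approximation is n = 2(1.960 + 0.842)² / d² = 15.70 / d² per group.

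- From the quoted changes, d = (0.08 − 0.028) / 0.09 = 0.052 / 0.09 = 0.578. Then n = 15.70 / 0.334 = 47.0, rounded up to 48 per group. With 24 per group, the two-sided t-test power is about 50%.
- From the stated target difference, d = 0.28 / 0.09 = 3.11. Then n = 15.70 / 9.68 = 1.6, rounded up to 2 per group.

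Neither gives 24. That is a separate problem with the sample size. It matters here for one reason: no power figure for an alpha split can be priced reliably from these inputs, so none is used below. The error rates do not depend on n.

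**Step 2: either outcome suffices.** With both null hypotheses true,

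FWER = 1 − P(|Z₁| ≤ 1.96 and |Z₂| ≤ 1.96), where Z₁ and Z₂ are bivariate normal with correlation ρ.

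For ρ = 0 this is 1 − 0.95² = 0.0975, or 0.0975 / 0.05 = 1.95 times the nominal level. For other values:

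| Correlation ρ | Family-wise error |
|---|---|
| 0 | 0.0975 |
| 0.3 | 0.0951 |
| 0.5 | 0.0907 |
| 0.7 | 0.0835 |
| 0.9 | 0.0704 |

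The tests are two-sided, so a negative correlation of the same size gives the same result. The error falls to 0.05 only when the two tests are perfectly correlated.

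**Step 3: both outcomes required.** The probability that both reject is never more than the probability that either one rejects on its own. The false positive rate is therefore at most 0.05, with no inflation. The same bound applies to power: joint power cannot exceed TSH's power, and it is lower unless fT4 is certain to succeed whenever TSH does. How much lower cannot be computed, because the protocol gives no effect or standard deviation for fT4.

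**Step 4: fixed sequence, TSH then fT4.** If the TSH null is true, any false claim requires a false rejection on TSH, with probability at most 0.05. If TSH has a true effect and fT4 does not, the only possible false claim is on fT4, again at most 0.05. The family-wise error is at most 0.05 at any correlation, and TSH keeps its full 0.05.

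**Step 5: number of tests under the primary objective.** There are 2 between-group comparisons plus 2 outcomes × 2 groups = 4 within-group comparisons, so 6 tests at 0.05. A success rule covering only the two between-group tests would leave the other four free to support a primary claim.

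**The case against.** The strongest reply is that a statistical analysis plan may exist and could state the success rule or the order. That has some force: the protocol shows an ambiguity and does not prove that an either-of-two rule is intended. It does not remove the point. The protocol is not silent but sets 0.05 for all analyses, and a plan that withheld significance from fT4 after a failed TSH test would depart from that sentence.

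A second reply is that the worst case needs two assumptions, independence and an either-of-two rule. This stands. The protocol presents the two hormones jointly as markers of thyroid function, so independence is not the natural assumption. A reader might infer that the error is simply double the stated level. The documents support only a range that depends on the correlation and the success rule.

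A reader might also count all six named outcomes (TSH, fT4, depression, quality of life, SBP and DBP) and infer an error of up to 1 − 0.95⁶ = 26%. The documents do not support that. Blood pressure, depression and quality of life are labelled secondary, and the hypothesis is a conjunction: "10 weeks of synbiotic supplementation will significantly improve serum levels of thyroid hormones, depression, quality of life, SBP and DBP in hypothyroid patients". It does not say that success on any one of them confirms it. Leaving labelled secondary outcomes unadjusted is common practice.

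Finally, fT4 need not be demoted to control the error. That is also correct, and the change proposed below does not require it.

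**Conclusion.** The point holds as a conditional one. The protocol has two unranked primary outcomes, a single 0.05 threshold and no success rule, so the error rate of its primary claim is not controlled.

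Under an either-of-two reading, the family-wise error is 7.0% to 9.75% for correlations from 0.9 down to 0, against a nominal 5%. This assumes two-sided tests and approximate normality of the test statistics. Under a both-required reading the error is at most 5%, and the stated 80% does not describe the trial's power because it was set for TSH alone.

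A reader might want a figure for the power lost under a both-required rule or an alpha split. The documents do not support one: fT4 has no stated effect or spread, and the TSH sample size does not follow from its own inputs.

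**What to change.** State a fixed sequence in Statistical methods, and align Objectives, Outcomes and Data collection methods with it:

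1. Test the between-group TSH comparison first, at two-sided 0.05.
2. Test the between-group fT4 comparison at two-sided 0.05 as confirmatory only if TSH is significant. Otherwise report it descriptively. fT4 may stay co-primary within this order or become the first secondary outcome.
3. State that within-group tests and the secondary outcomes (SBP, DBP, BDI-II, SF-36) are supportive, reported with estimates and 95% confidence intervals, and do not carry the primary claim.
4. Limit the general P < 0.05 sentence accordingly.

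TSH goes first because it is the outcome on which the trial was sized. The order should be fixed before the treatment codes are opened.

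The cost is that fT4 can no longer succeed alone, and that an amendment is needed, which under Protocol Amendments requires ethics committee approval. The registered description should be kept in line. The change needs no extra patients, no extra data and no loss of power for TSH. It does not repair the sample size calculation, which needs separate attention.

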**Eligibility criteria**

Inclusion criteria

Women or men (25-55 years old) with subclinical hypothyroidism (elevated TSH level and a normal or low free T4 level) for at least a year, and BMI less than 35 who are being treated by levothyroxine. Voluntary written informed consent for all patients is mandatory before any study related procedures.

Exclusionary criteria

The participants must not have any of the following: lactating or pregnant; History of taking probiotic or synbiotic supplements in the last three months; Smoking or alcohol consumption; Taking appetite suppressants such as antibiotics; Use of antibiotics and any medications that interact with synbiotics; Gastrointestinal diseases such as stomach ulcers, diarrhea or constipation etc. for three months before or during the intervention; unwillingness to continue cooperation, non-compliance during the intervention, or no signed informed consent. Participants will also be excluded in case of providing incomplete questionnaires (more than 40% of the dietary questionnaire is incomplete), catching infectious diseases such as Covid-19 during the study, occurrence of pregnancy, undergoing surgery, occurrence of a change in the dose or type of medication, consumption of foods enriched with probiotics (e.g. probiotic yoghurt) during the study.

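### The primary between-group TSH comparison has no stated scale, no non-normal alternative and no named baseline-TSH covariate, so it may lose power if TSH is strongly right-skewed

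*Protocol*

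**What the plan says.** All of this is in the Protocol.

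- **Objectives.** The primary objective compares mean changes in FT4 and TSH between and within groups. A list of variables to be treated as confounders follows (among them age, BMI, diet, levothyroxine dose and type of hypothyroidism). Baseline TSH is not on it.
- **Eligibility criteria.** Entry requires "elevated TSH level and a normal or low free T4 level". No numerical TSH limit, lower or upper, is given.
- **Statistical methods, descriptive.** Normality is checked by Shapiro-Wilk and by P-P and Q-Q plots. The summary is the same for everything: "All variables will be reported as mean ± SD for before, after the intervention and changes (after minus before").
- **Statistical methods, within groups.** Change from baseline "will be illustrated through a paired t-test or Wilcoxon signed-rank test".
- **Statistical methods, between groups.** The independent t-test is assigned to baseline characteristics. After baseline the only named method is: "Analysis of Covariance (ANCOVA) will be performed to eliminate the effect of confounders".
- **Sample size.** The plan works with a raw mean change, a raw SD and a target of 0.28 mIU/L.

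**The concern.** The between-group comparison is the randomised one and answers the primary question, yet it has the thinner specification. The authors foresaw non-normal data and wrote an alternative for the within-group test, but not for this one.

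Two things are at stake. First, TSH cut off from below at entry and open at the top plausibly has a right tail. With about 24 evaluable patients per arm, a few high values could then weigh heavily on a raw mean, an SD and the ANCOVA residuals, and cost power. Second, if the planned normality check fails for TSH, the protocol does not say whether ANCOVA stands or what changes, so that decision could be made after seeing the data.

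**Working it through.** **1. What is fixed for each comparison**

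| Comparison | Method named | If normality fails |
|---|---|---|
| Baseline, between groups | independent t-test; chi-square for qualitative variables | not stated |
| Change within a group | paired t-test | Wilcoxon signed-rank |
| After baseline, between groups (primary) | ANCOVA for confounders | not stated |

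**2. The plan's own sample size, as a possible anchor for power**

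Inputs: "the probability of the first type error equal to 0.05 (α = 0.05, significance"); "the probability of the second type error equal to 0.80 (β = 0.2, power"), read as 80% power; changes of "0.08 ± 0.09 mIU/L and 0.028 ± 0.09 mIU/L, respectively"; and the target, "in order to observe 0.28 mIU/L difference in serum TSH levels between the two groups at the end of the study". Stated result: 24 per group.

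n per group = 2 × (1.96 + 0.84)² × (SD/difference)² = 15.7 × (SD/difference)².

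- Difference 0.28, SD 0.09: 15.7 × 0.103 = 1.6, so 2 per group (3 by the t distribution).
- Difference 0.08 − 0.028 = 0.052, SD 0.09: 15.7 × 3.00 = 47, so 48 after rounding up with exact quantiles (49 by the t distribution). Power at 24 per group is 50–52%.
- 24 per group for 0.28 needs an SD of about 0.33–0.34 (two-sided), which the document does not give.

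The stated 24 is not reproduced. That is a separate problem. Here it means that there is no sound planned power from which to subtract a loss, so the effect of scale must be shown under stated assumptions.

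**3. Power at 24 per arm by scale**

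None of the distributional inputs below is in the document; all are assumptions.

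*Proportional error and effect (log-normal TSH)*

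| Setting | Raw ANCOVA | Log ANCOVA | Log minus raw |
|---|---|---|---|
| A. Entry above 4.5 mIU/L; between-patient log-SD 0.35–0.7; within-patient log-SD 0.2–0.3; effect 16–22%; 3,000 trials per scenario | 44–56% | 54–59% | 3 to 10 points |
| B. Baseline cut from below; correlation 0.7; log-SD 0.4 | 76% | 78% | 2 |
| B, log-SD 0.6 | 74% | 79% | 5 |
| B, log-SD 0.8 | 70% | 79% | 9 |
| B, log-SD 1.0 | 65% | 79% | 14 |
| C. True median 3; log-SD 0.35–0.7; entry above 4.5; effect 20%; 1,500 trials per scenario | – | – | 2 to 7 |
| D. Entry above 4.5; log-SD 0.35–0.7 | – | – | 2 to 8 |

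B uses 5,000 trials per row and an effect of 0.826 residual log-SDs, so the assumed effect grows with the log-SD. The residual log-SD is log-SD × √(1 − 0.7²) = 0.714 × log-SD. At log-SD 0.4 the ratio is exp(−0.826 × 0.286) = 0.79, a 21% fall. At 1.0 it is exp(−0.826 × 0.714) = 0.55, a 45% fall. The 14-point row therefore rests on both extreme skew and a very large effect, so 2 to 10 points is the fairer range.

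*Additive error with constant SD*

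| Setting | Raw ANCOVA | Log ANCOVA | Log minus raw |
|---|---|---|---|
| C with error SD 1.0 and effect 0.8 mIU/L | 51, 49, 49% | 46, 44, 42% | −5, −5, −7 |
| D with additive error | – | – | −1 to −5 |

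Simulation standard error of one power figure is about √(0.25/1,500) = 1.3 points in C and √(0.25/3,000) = 0.9 points in A. Gaps of 1 or 2 points are not informative.

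**4. Baseline adjustment**

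In D, raw ANCOVA with baseline TSH gained 5 to 10 points over a t-test of raw change under proportional error, and was within about 1 point of it under additive error. In A the t-test of raw change had 37–49% power.

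**5. Type I error**

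About 5% for all three methods in A. For raw ANCOVA it was 4–5% in the null runs of B, which had no entry cut.

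**The case against.** A reader might infer that TSH will be analysed only on the raw scale, that skew follows from the entry rule, and that the comparison therefore loses power. The documents support none of these outright.

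- **Scale.** The mean ± SD sentence concerns reporting. The scale of the ANCOVA is never stated, and a statistical analysis plan that is not shown could settle it. This stands as a limit on the wording. It does not dissolve the point: the protocol does not leave the topic open, because it sets the summary for every variable, names the between-group method and writes a non-normal alternative for the less important test only.
- **Skew.** No TSH limit, mean or log-scale SD is given. The entry cut acts on baseline TSH, which would be the covariate, whereas ANCOVA depends on residuals. Cutting from below also shrinks the loss: at log-SD 0.6 and correlation 0.7, raw versus log power is 74% against 79% with the cut, and 69% against 79% without it. This stands; a right tail is plausible, not established.
- **Power.** The loss depends on proportional error, and under additive error its sign reverses. The assumed effects are also far from the planning figures. At 4.5 mIU/L, 16–22% is 0.72–0.99 mIU/L, about 2.6–3.5 times 0.28. A within-patient log-SD of 0.2 implies an SD of change near 4.5 × 0.2 × √2 = 1.3, about 14 times 0.09. This stands, with the reservation that those planning figures do not agree with each other.
- **Estimand.** A ratio of geometric means is not a comparison of mean changes. This stands, and is a cost of the fix.

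**Conclusion.** The point holds as a gap in specification with a conditional cost. The normality check has a consequence only within groups. The primary between-group TSH comparison has no stated scale, no non-normal alternative and no named baseline-TSH covariate.

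If TSH is log-normal with proportional error and effect, a raw-scale ANCOVA at 24 per arm gives up about 2 to 10 points of power, at the low end when skew is mild. If error is additive with constant SD, the log scale gains nothing and may lose a few points (1 to 7 in the runs above). The case for naming baseline TSH as a covariate is firmer, since it gained 5 to 10 points over an unadjusted comparison of raw change in one error structure and cost almost nothing in the other.

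Two stronger readings should be resisted. The analysis is not invalid, since type I error stayed at 4–5%. Nor does the protocol say that ANCOVA would be dropped if normality failed; it is silent on that. This is a cheap improvement of low to moderate severity.

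**What to change.** In Statistical methods, state before any outcome data are seen:

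- The primary TSH analysis is ANCOVA of log(TSH) at week 10 on group and log(baseline TSH), reported as a ratio of geometric means with 95% CI.
- TSH is also summarised by geometric mean or median (IQR), next to mean ± SD.
- Raw-scale ANCOVA with baseline TSH as covariate is a sensitivity analysis. It covers the case of additive error and keeps a result in mIU/L.
- The Shapiro-Wilk result does not choose the primary test.

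**Cost.** About one sentence in the methods and no new data. The effect becomes a ratio, so the mean-changes wording in Objectives and the 0.28 mIU/L target in Sample size must also be expressed on that scale. The conversion depends on baseline TSH: at an assumed 4.5 mIU/L, 0.28 corresponds to (4.5 − 0.28)/4.5 = 0.94, and at higher baselines the ratio is closer to 1. If error proves additive, a few points of power may be given up.
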